## Abstract

A remarkable, yet poorly explained feature of Systemic Lupus Erythematosus (SLE) is the propensity to flare following a preceding period of disease inactivity. The clinical burden of lupus flares is substantial since they often tend to involve multiple or major organs, and carry a near two-fold increased risk for accrual of irreversible organ damage. The cellular and molecular mechanisms underlying the progression of SLE from inactive to active state remain ill-defined. Application of novel sequencing technologies together with cellular immunology assays, have illustrated the important role of multiple types of both innate and adaptive cells and associated pathways. We have previously described significant differences in the blood transcriptome of SLE patients at active versus inactive disease, and we have also defined genome regions (domains) with co-ordinated expression of genes implicated in the disease. In the present study, we aim to decipher the cellular and molecular basis of SLE exacerbations by utilising novel single-cell sequencing approaches, which allow us to characterise the transcriptional and epigenetic landscapes of thousands of cells in the peripheral blood of patients. The significance of the study lies in the detailed characterisation of the molecular and regulatory program of immune cell subpopulations that underlie progression from inactive to active SLE. Accordingly, our results may be exploited to identify biomarkers for disease monitoring and novel therapeutic targets.

## BACKGROUND AND STUDY RATIONALE

One of the intriguing characteristics of Systemic Lupus Erythematosus (SLE) is its tendency for increases in disease activity, also known as flares, which are often unpredictable. Indeed, in various patient cohorts, the frequency of SLE flares (or relapses) is approximately 0.30–0.50 per patient-year, and despite available treatments, long-term disease quiescence occurs only in a small fraction of patients.^1^ The clinical burden of lupus flares is remarkable, since about 30–40% of exacerbations affect multiple or major organs (for instance, kidneys), they necessitate treatment escalation or switch (including administration of high-dose glucocorticoids or other potent immunosuppressives), and are linked to almost 2-fold increased risk for irreversible organ damage.^2,3^ Importantly, treatment of SLE relapses remains empirical due to lack of randomised evidence and personalised options based on the underlying pathophysiology.

The cellular and molecular mechanisms implicated in SLE re-activation following a previous period of quiescence remain elusive.^4^ During recent decades, the advent of next-generation genome sequencing technologies coupled with focused cellular immunology studies, have provided unique insights regarding the role of specific cell types of both innate (eg, neutrophils) and adaptive (eg, follicular helper T-cells, long-lived plasmablasts) immunity as well as of pertinent pathways (eg, interferon-alpha, autoantibodies) in SLE pathogenesis.^5–10^

To this end, the gene expression and functional state of cells may be altered under the effect of exogenous or other (for instance, inflammatory cytokines) factors through epigenetic changes including histone and chromatin modifications.^11,12^ In fact, changes in the epigenetic and transcriptional program of tumour-surveilling immune cells have been linked to resistance to chemotherapy and progression of malignant disease.^13,14^

In a previous work using RNA-sequencing (RNA-seq), we identified widespread perturbations in gene expression in the peripheral blood of active SLE patients as compared to their counterparts at remission or low disease activity state.^15^ A total of 693 genes showed differential expression in patients with active versus inactive or low disease activity, and these genes were enriched in pathways such as type I interferon, proteasome, and oxidative phosphorylation. Further analysis revealed that genomes of SLE patients are organised into distinct regions of co-expressed genes (known as *Domains of Coordinated gene Expression [DCEs]*), which seem to regulate important pathways, such as interferon.^16^ These DCEs varied according to the level of SLE activity and correlated with changes in chromatin accessibility. Notably, the genomes of patients at low disease activity or remission displayed co-expression of genes implicated in kidney disease and neutrophil activation, which suggests the persistence of genomic aberrations contributing to disease flare-up.

Furthermore, other research groups have described alterations in chromatin accessibility and/or activation of gene enhancers in SLE patient-derived monocytes,^17,18^ neutrophils^19^ and B-cells.^20,21^ Altogether, these data underscore a possible role of the chromatin environment and epigenetic factors on determining the transcriptional program and function of immune cells contributing to lupus. Still, the time-dynamics of the aforementioned molecular cues and the interaction between various immune cell types have not been studied in the context of SLE transition from inactive to active state.

## AIMS OF THE STUDY

In this research study, we aim to investigate the cellular and molecular basis of flares in patients with SLE. Considering the complexity of the disease, we will utilise state-of-the-art single-cell sequencing technologies to obtain a detailed map of the transcriptional and epigenetic profiles in multiple subtypes of peripheral blood immune cells. Through a prospective biosampling protocol, we plan to simultaneously characterise gene expression and chromatin accessibility at single-cell resolution in the peripheral blood mononuclear cells (at least 3,000 to 5,000 cells per patient sample) from two (2) SLE patients assayed at three (3) consecutive time points: disease remission, flare and post-flare (after treatment modification). Our hypothesis is that specific epigenetic modifications (chromatin accessibility) direct the molecular reprogramming of specific immune cells thus contributing to SLE relapse.

## METHODS

This is a prospective, non-interventional, clinical-translational study with the following design and implementation plan.

### Patient recruitment

Patients diagnosed with SLE will be screened consecutively and recruited from the Connective Tissue Disease out-patient clinic of the Rheumatology Department, University Hospital of Heraklion, Greece. Inclusion criteria will include: a) fulfilment of the 2019 EULAR/ACR (European Alliance of Associations for Rheumatology / American College of Rheumatology) classification criteria,^22^ b) age 18–40 years, c) history of positive anti-dsDNA autoantibodies, d) relapsing-remitting disease pattern,^23^ and e) low disease activity or remission during the past 3 months according to the LLDAS^24^ and DORIS25 definitions, respectively. Exclusion criteria will include: a) coexistence of other systemic autoimmune or inflammatory disease, b) pregnancy or planning for pregnancy, c) chronic infection, d) history of malignancy, e) treatment with cyclophosphamide during the previous 3 months or with rituximab during the previous 6 months. The study will receive approval by the Institutional Review Boards of the University Hospital of Heraklion and the University of Crete, and all participants will provide informed consent form.

### Sample size

Considering that single-cell technologies enable the profiling of thousands of individual cells (up to 10,000 cells per sample) from peripheral blood samples, a relatively small number of patients is adequate. Since this is a pilot study, only two (2) patients will be analysed, each patient sampled on three consecutive time points: during remission or low disease activity, at the time of flare, 3 months post-flare and after treatment administration.

Patient samples of each time point will be combined and profiled in a separate 10x Multiome library. To identify two eligible patients, a total 20 SLE patients who meet the aforementioned inclusion criteria will be monitored clinically over a period of 12 months.

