### Isolation of peripheral blood mononuclear cells and single-cell RNA-seq/ATAC-seq

We will assay blood as a relevant and easily accessible tissue to define complex inflammatory signatures.^29,30^ Venous samples (2 patients x 3 time-points, 6 in total) will undergo Ficoll density centrifugation for isolation of peripheral blood mononuclear cells (PBMCs). In SLE, the PBMCs fraction also includes circulating neutrophils,^31^ which are relevant to disease pathogenesis. Single-cell suspensions will be prepared on microplates through the robotic Fluidigm C1 system, followed by purification of RNA and chromatin from the cell nuclei.^32^ Genomic material will be processed for library synthesis (DNA for chromatin, cDNA for gene expression) and analysis by the chromium-based (10x) single-cell multiome ATAC (Assay for Transposase-Accessible Chromatin) & gene expression.^32–34^ Next-generation sequencing will be carried out at the Genomic Facility, IMBB-FORTH.

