### Bioinformatics and data analysis

We will create a single-cell transcriptomic and epigenomic atlas followed by modularity optimisation to detect immune cell clusters across patient groups and time-points.^35,36^ Differential gene expression between pertinent immune cell clusters, coupled with functional enrichment analysis, will characterise the cellular states and dedicated transcriptional programs predisposing to flares. Chromatin accessibility data will help to disentangle the regulatory programs governing the transition to active SLE, guided by the cell-to-cell linkage between modalities (scRNA-seq, scATAC-seq) and the cell-state annotations of the transcriptome atlas. Using the scATAC-seq data, we will characterise our immune cell clusters, and determine high resolution cell sub-clusters with unique chromatin accessibility profiles. Open chromatin regions (OCRs) will be subjected to functional enrichment analysis (LOLA, GREAT tools) to infer their putative regulatory roles.^37,38^ Also, mapping of transcription factor (TF) binding sites (TFBS) motifs^39^ will reveal enrichment of specific TFs involved in the acquisition of a primed state of immune cells. Correlation between gene expression, TF expression and motif accessibility will identify flares-predisposing Gene Regulatory Networks (TF-to-gene promoter/enhancer relationships). Finally, reconstruction of immune cell lineage differentiation and cell maturation trajectories will delineate the cellular dynamics and underlying states during SLE re-activation*.*^35,40^ Collectively, our analysis will decipher how gene regulatory reprogramming in immune cells triggers flare initiation. We will also test the reversibility of these molecular/regulatory programs in the post-flare samples.

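### Cell numbers are used to call a small number of patients adequate, but the patient is the replicate: with n = 2 the time-point comparisons are descriptive and cannot support a general statement about how flares start

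*Protocol article*

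**What the plan says.** The Sample size section gives two reasons, one after the other.

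- The first is technical: "Considering that single-cell technologies enable the profiling of thousands of individual cells (up to 10,000 cells per sample) from peripheral blood samples", it follows that "a relatively small number of patients is adequate".
- The second is the type of study: "Since this is a pilot study", "only two (2) patients will be analysed, each patient sampled on three consecutive time points".

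The Aims section sets a floor of "at least 3,000 to 5,000 cells per patient sample". No alpha, power, effect size or between-patient variance is given. The Sample size section also pools the patients' samples from each time point into one library, with a separate library for each time point.

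The Bioinformatics and data analysis section plans "Differential gene expression between pertinent immune cell clusters, coupled with functional enrichment analysis" and does not name the unit of analysis. It closes with an unhedged promise to explain how changes in gene regulation within immune cells set off a flare, and it adds a test of whether those changes reverse after treatment. The Abstract is more cautious: "our results may be exploited to identify biomarkers for disease monitoring and novel therapeutic targets".

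**The concern.** The number of cells and the number of patients answer different questions. Cells from one draw share that patient's genetics, medication, sample handling and disease state on that day. Sequencing more of them gives a better picture of that draw. It says nothing about how the change from remission to flare varies from one patient to the next, and a statement about flares in SLE rests on that variation.

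The first reason therefore credits the design with a property it lacks. The risk is that a large cell count is taken as support for general conclusions. Patterns particular to two people, or to single draws, could then be carried forward as features of lupus flares and as candidate biomarkers or targets.

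**Working it through.** **1. The plan's own figures.** The figure n = 2 has no error rate, effect size or variance behind it, so no formula can reproduce it. What can be checked is the number monitored: 20 patients over 12 months (Sample size) at 0.30 to 0.50 flares per patient-year (Background). Assume a constant rate and that any flare counts.

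- Chance that a patient flares: 1 − exp(−0.30) = 0.259; 1 − exp(−0.50) = 0.393.
- Expected flaring patients: 20 × 0.259 = 5.2; 20 × 0.393 = 7.9.
- Chance of at least two among 20 (binomial): 0.980 to 0.999.

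So 20 is enough to find two patients. It does not show that two are enough.

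**2. What n = 2 gives at patient level.** This step needs no assumption about correlation between cells. For each patient take one change per gene and cell type, flare minus remission.

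- Degrees of freedom: 2 − 1 = 1; critical t (two-sided 5%) = 12.71.
- 95% confidence interval half-width: 12.71 / √2 = 9.0 standard deviations of the patient-level change.
- Smallest two-sided sign-test p-value: 2 × 0.5² = 0.50.
- Power of one unadjusted paired t-test (noncentral t) for an assumed mean change of 1, 2 or 3 standard deviations: 9%, 18% and 26%. Reaching 80% would take about 10, 5 and 4 patients, before any correction for the number of genes.

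**3. What more cells add.** Let m be the cells per sample in a cluster, and ICC the share of a gene's variance that lies between samples (patient by time point). The article gives neither, so both are assumptions. The design effect is DE = 1 + (m − 1) × ICC, and the effective number of cells is m / DE, which cannot exceed 1 / ICC.

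| ICC | m = 500 | m = 10,000 | Ceiling 1/ICC |
|---|---|---|---|
| 0.01 | 500 / 5.99 = 83 | 10,000 / 100.99 = 99 | 100 |
| 0.05 | 500 / 25.95 = 19.3 | 10,000 / 500.95 = 20.0 | 20 |

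At these values a twentyfold increase in cells adds little.

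**4. Conditional check: if cells were the unit of testing.** With no true time effect, a nominal 5% two-sided test rejects with probability 2 × [1 − Φ(1.96 / √DE)].

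| ICC | m = 100 | m = 500 | m = 3,000 |
|---|---|---|---|
| 0.001 | 0.06 | 0.11 | 0.33 |
| 0.01 | 0.17 | 0.42 | 0.73 |
| 0.05 | 0.42 | 0.70 | 0.87 |

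A simulation with two patients and two time points gave 0.43 (ICC 0.01) and 0.68 (ICC 0.05) at m = 500. A paired t-test on patient means stayed at 4% to 6% in the same simulations. The inflation grows with m, the quantity on which the adequacy argument relies.

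**5. Agreement between the two patients.** For a gene with no true change, the two patients' changes agree in direction with probability 0.5² + 0.5² = 0.50. Because each time point has its own library, a library effect would also move both patients the same way and look like agreement.

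**The case against.** The strongest defence is that the study calls itself a pilot, and that this label, not the cell count, is the reason given for exactly two patients. The cell-count sentence supports only a small number in general. Much of the aim is also descriptive, a map or atlas of cell states, and many cells from few patients can serve that aim. The Abstract's remarks on biomarkers and targets are hedged. All of this stands, and it justifies n = 2 for description. It does not make the step from cells to patients valid, and it does not cover the firm causal promise at the end of the analysis section.

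Three stronger readings are tempting, and the document does not support them.

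- A reader might infer that the plan commits to cell-level testing, or that this is the only sense in which two patients could be adequate. The analysis section neither states nor excludes it, and a condensed article may leave the unit of testing to a fuller document.
- A reader might infer that false-positive rates will be many times nominal. That depends on an assumed ICC and cluster size. At ICC 0.001 with 100 to 500 cells the rate is only 6% to 11%.
- A reader might infer that a third flaring patient would fit into the same libraries. The figure of up to 10,000 cells is stated per sample, not per library. If it were a library limit, 10,000 / 3 = 3,333 nuclei per patient before quality control would leave little margin above the 3,000 floor.

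**Conclusion.** The concern holds as an error in the stated rationale and in the reach of the conclusions. The protocol infers that few patients are adequate from a quantity that does not bear on replication between patients. The 1 degree of freedom, the half-width of 9.0 standard deviations and the minimum sign-test p-value of 0.50 follow from n = 2 alone. On that basis the design cannot support a general statement of how flares are triggered, though it can describe two patients in detail and generate hypotheses.

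The error-rate range of about 11% to 70% is conditional. It applies only if cells are tested as independent units, and it assumes 500 cells per cluster and ICCs of 0.001 to 0.05. It is a reason to rule that analysis out, not a finding that it is planned.

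**What to change.** 1. Replace the adequacy sentence. Suggested text: *The number of patients analysed (n = 2) is set by the feasibility of a pilot study. Profiling many cells improves precision within each sample but does not replicate patients. Comparisons between time points are therefore descriptive and hypothesis-generating.* Soften the closing claims of the Bioinformatics and data analysis section to match, including the test of reversibility.
2. State the unit of analysis for time contrasts. Assign cells back to patients within each pooled library, aggregate counts by patient, time point and cell type (pseudobulk), and report each patient's own changes between time points. Give no cell-level p-values for these contrasts. The means of assigning cells to patients must be settled before samples are pooled.
3. Treat agreement between the two patients as descriptive only, and say why: direction agrees by chance half the time, and library coincides with time point. Pseudobulk does not remove a library effect.

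The cost is a change of wording and a standard aggregation step. The downside is far fewer nominally significant genes and more modest conclusions.

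### Pooling both patients' samples by time point into one library each means that differences between remission, flare and post-flare cannot be separated from library effects

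*Protocol article*

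**What the plan says.** The Sample size section says that "only two (2) patients will be analysed, each patient sampled on three consecutive time points", the time points being "during remission or low disease activity, at the time of flare, 3 months post-flare and after treatment administration". It then fixes the library layout: "Patient samples of each time point will be combined and profiled in a separate 10x Multiome library". The section on cell isolation and sequencing confirms the count: "Venous samples (2 patients x 3 time-points, 6 in total) will undergo Ficoll density centrifugation". The natural reading is three libraries, each holding one sample from each patient, all at the same disease state.

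The analysis then depends on comparing states. Bioinformatics and data analysis plans "modularity optimisation to detect immune cell clusters across patient groups and time-points" and a test of whether the flare programs reverse in the post-flare samples. Anticipated results looks for cell sub-populations whose frequency or functional state changes during flare. The article describes no sample shared between libraries and no pooling across time points.

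**The concern.** Libraries can differ for technical reasons such as nuclei loading, transposition efficiency, ambient RNA and depth. Under the stated layout any such difference is also a difference between disease states, and an analysis plan cannot undo this once the libraries are made.

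With two patients, agreement between them is the only biological replication. Pooling by time point does balance patients within library, which protects the comparison between patients. But the study is about the comparison between states, and there a library artefact moves both patients in the same direction and passes for a replicated finding.

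**Working it through.** **Inputs.** 2 patients (A, B) and 3 states, hence 2 × 3 = 6 samples, which matches the article's total. Three libraries, one per time point (Sample size). The article gives no alpha, power, effect size or library variance.

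**Stated layout.** For patient p at state t, let y = μ + π(p) + τ(t) + λ(library) + e, with Var(e) = σ². Library equals state, so the average flare–remission difference over the two patients estimates [τ(flare) − τ(rem)] + [λ(2) − λ(1)]. The design matrix has 1 + 1 + 2 + 2 = 6 columns. The two library columns repeat the two state columns, so the rank is 4. All three state contrasts are non-estimable once library is allowed for; the patient contrast is estimable.

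**By cell type.** With two cell types, a state × cell-type term and an additive library effect, there are 9 columns and rank 7. The state contrast within each cell type is still non-estimable. The state × cell-type difference is estimable, provided that the library effect is the same in both cell types.

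**False replication.** Let a fraction s of sample-level noise variance be shared within a library, with no true state effect. The flare–remission differences of A and B then have correlation r = s under the stated layout. Select features with z > 1.96 in A. The chance of the same sign in B is P(Z_B > 0 | Z_A > 1.96) for a bivariate normal with correlation r. In the crossed layout below, A's difference carries λ2 − λ1 and B's carries λ1 − λ3, so r = −s/2.

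| s (assumed) | Stated layout | Crossed layout |
|---|---|---|
| 0 | 50% | 50% |
| 5% | 55% | 48% |
| 10% | 59% | 45% |
| 25% | 73% | 38% |
| 50% | 91% | 27% |
| 75% | 99% | 17% |

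**More cells do not help.** As an illustration, assume 500 cells per sample in a cluster, unit cell-level SD and no true effect. A cell-level 5% test of flare against remission has SE = √(2/1000) = 0.045. With library SD L, the rejection rate is 2Φ(−1.96·SE/√(2L² + SE²)). For L = 0, 0.05, 0.1, 0.2 and 0.5 this gives 5%, 29%, 55%, 76% and 90%. More cells shrink SE but not L, so the rate rises.

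**Crossed layout.** Library 1 = A remission + B flare; library 2 = A flare + B post-flare; library 3 = A post-flare + B remission. There are 6 columns and rank 6. The flare–remission estimate is (1/3)[−2·A_rem + A_flare + A_post − B_rem + 2·B_flare − B_post]. Library terms cancel: library 1 has weights −2/3 and +2/3, and libraries 2 and 3 each have +1/3 and −1/3. The variance is (4+1+1+1+4+1)/9 = 1.33σ², against (2σ² + 2σ²)/4 = 1.00σ² for the mean paired difference if there were no library effects. Residual df = 6 − 6 = 0. Adding a patient × time interaction gives 8 columns and rank 6, and the state contrast is again non-estimable.

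**Other layouts.** A patient's three time points in one library, or all six samples in one tagged pool: state contrasts estimable, variance 1.00σ², 2 residual df. One library per sample: 9 columns, rank 6, state contrasts still non-estimable.

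**The case against.** Several points can fairly be made for the plan.

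- A reader might infer that the state contrasts cannot be estimated at all, or that the whole analysis fails. The article does not support that. The raw differences can be computed. Differential expression is worded as a comparison between clusters, which can be made within a library, and links between transcription factors and genes can use within-library information. This stands, and it limits the point to main state shifts, cell frequency and reversibility.
- The rank result shows dependence on an assumption, not the size of any artefact. One library per sample fails the same test. This stands: the documents give no library variance, so quoting a single figure such as 91% would overstate what is known. The table runs from near chance to near certainty.
- Some differences, such as sequencing depth, are observed and can be equalised, and preparing stored samples together would shrink others. Both are true, but neither breaks the aliasing. Integration methods need untestable assumptions, for example stable reference populations.
- This is a two-patient pilot, and a condensed article may leave session planning and bridging controls to the full protocol. That is reasonable for detail that is absent, but the layout of one library per time point is stated outright.
- Crossing does not cure everything. If λ2 > λ1 > λ3, both patients still show a spurious rise, and crossing aliases library with patient × time. This stands and is reflected in the fix.

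**Conclusion.** The concern holds in this form: under the stated layout library and disease state are completely aliased, so differences between remission, flare and post-flare cannot be separated from library effects. The aliasing follows from the Sample size section alone and needs no assumption. Its consequence depends on the unknown library effect: chance agreement in sign between the patients is about 55% at 5% shared noise and 99% at 75%, against 50% with none. These figures assume normal noise, no true effect and selection at z > 1.96.

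It would go too far to say that an artefact is present, that no analysis survives, or that crossing removes every spurious agreement. Within-library cluster comparisons are unaffected, as are state × cell-type differences under a common library effect. The point still deserves correction because it touches the study's main comparison, cannot be repaired once libraries exist, and costs little to change beforehand.

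**What to change.** Change the library sentence in Sample size so that time points are crossed over the same three libraries, for example A remission + B flare, A flare + B post-flare, A post-flare + B remission. Prepare all three in one session from stored samples. Each library still holds one sample per patient, so nuclei can be assigned to patient by genotype. State contrasts become estimable in an additive patient + state + library model, and a library artefact no longer favours agreement between the patients, though it can still produce some.

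**Cost.** No extra patients, samples or libraries. Pooling by time point already implies holding samples, since the two patients are unlikely to flare together, but no library can now be completed until its later sample arrives, and a single session waits for the last of the six. The flare–remission variance is 1.33σ² instead of 1.00σ². The additive model is saturated and assumes no patient × time interaction, so the library-adjusted analysis cannot itself test agreement between patients, and results stay descriptive.

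**Better, if sample tagging is feasible.** Put all three time points of a patient in one library, or all six samples in one tagged pool. This keeps variance 1.00σ² and 2 residual df. Tagging is needed because genotype cannot separate samples of the same patient. Merely splitting into one library per sample is not a remedy.

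**If the stated layout is kept,** the article should say that differences between states are not separable from library effects, and present them on that footing.
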